## Abstract

Repurposed drugs are important in resource-limited settings because the interventions are more rapidly available, have already been tested safely in other populations and are inexpensive. Repurposed drugs are an effective solution, especially for emerging diseases such as COVID-19. The REVOLUTIOn trial has the objective of evaluating three repurposed antiviral drugs, atazanavir, daclatasvir and sofosbuvir, already used for HIV- and hepatitis C virus-infected patients in a randomized, placebo-controlled, adaptive, multiarm, multistage study. The drugs will be tested simultaneously in a Phase II trial to first identify whether any of these drugs alone or in combination reduce the viral load. If they do, a Phase III trial will be initiated to investigate if these medications are capable of increasing the number of days free respiratory support. Participants must be hospitalized adults aged ≥ 18 years with initiation of symptoms ≤ 9 days and SpO_2_ ≤ 94% in room air or a need for supplemental oxygen to maintain an SpO_2_ > 94%. The expected total sample size ranges from 252 to 1,005 participants, depending on the number of stages that will be completed in the study. Hence, the protocol is described here in detail together with the statistical analysis plan. In conclusion, the REVOLUTIOn trial is designed to provide evidence on whether atazanavir, daclatasvir or sofosbuvir decrease the SARS-CoV-2 load in patients with COVID-19 and increase the number of days patients are free of respiratory support. In this protocol paper, we describe the rationale, design, and status of the trial.

**ClinicalTrials.gov identifier:** NCT04468087

## INTRODUCTION

### Background and rationale

Coronavirus disease 2019 (COVID-19) reached a pandemic status, and several approaches have been suggested to control severe acute respiratory syndrome coronavirus 2 (SARS-CoV-2) replication in patients with moderate to severe cases. One of these strategies includes the repurposing of antiviral drugs used to treat severe acute respiratory syndrome coronavirus 1 (SARS-CoV-1) and Middle East respiratory syndrome coronavirus (MERS-CoV), including antiretroviral agents.^(1)^ Drugs such as remdesivir, lopinavir and ritonavir, darunavir and cobicistat, umifenovir and oseltamivir potentially exert therapeutic effects against COVID-19.^(2)^ However, among these repurposed drugs, only remdesivir showed clinical benefits for COVID-19 treatment.^(3)^

Other specific and nonspecific antivirals have been proposed to treat the disease. Some are based on the results from in vitro and clinical studies conducted with a small sample size in specific populations. Atazanavir (ATV) blocked the major protease activity of SARS-CoV-2 in a protease-free cell assay;^(4)^ sofosbuvir (SOF) showed EC_50_ values against SARS-CoV-2 replication of 6.2 and 9.5µM in HuH7 (hepatoma) and Calu-3 (type II pneumocytes) cells, respectively;^(5)^ and daclatasvir (DCV) consistently inhibited the production of SARS-CoV-2 infectious particles in Vero cells, the HuH-7-cell line and Calu-3 cells, preventing the induction of interleukin (IL) 6 and tumor necrosis factor alpha (TNF-α) production.^(5)^ Available clinical studies are synthesized in recent meta-analysis, SOF/DCV may reduce the mortality rate and need for intensive care unit (ICU)/invasive mechanical ventilation (IMV) in patients with COVID-19 while increasing the chance for clinical recovery with a low to moderate quality of evidence.^(6)^ However, no studies investigating DCV or ATV alone have been published.

Implementing studies that allow more than one new treatment to be tested simultaneously may be advantageous over classic parallel group studies. The main objectives of this type of clinical trial are to quickly reject any new therapies that do not seem to be better than controls and to identify those that are significantly better in terms of clinical outcomes.^(7)^ Thus, we propose a randomized, placebo (PbO)-controlled, adaptive, multiarm, multistage Phase II trial to evaluate ATV, DCV and DCV plus SOF simultaneously to first identify whether any of these drugs alone or in combination reduce the viral load. If they do, a Phase III trial will be initiated to investigate clinical outcomes.

### Objectives

The main objective of the REVOLUTIOn trial is to evaluate whether repurposed antiviral drugs alone or in combination are effective at decreasing the viral load and increasing the number of days free of respiratory support. The primary and secondary objectives are described in table 1.

**Table 1 t1:** Objectives and outcomes

Primary objective	Outcome/primary variables
Phase II first stage (II/1): compare the effect of treatment with single antivirals against placebo in reducing the load of SARS-CoV-2 in nasopharyngeal swab samples	Decay rate (slope) of the SARS-CoV-2 viral load logarithm in nasopharyngeal and swab samples evaluated at D0, D3, D6 and D10 after randomization
Phase II second stage (II/2): compare the effect of treatment with combinations of antivirals compared to isolated ones in reducing the SARS-CoV-2 viral load in nasopharyngeal swab samples	Decay rate (slope) of the SARS-CoV-2 viral load logarithm in nasopharyngeal and swab samples evaluated at D0, D3, D6 and D10 after randomization
Phase III: compare the efficacy of antivirals alone or in combination to the placebo in increasing the number of days free of respiratory support	Days free of respiratory support, defined as the number of days without oxygen, noninvasive ventilation/high-flow nasal cannula or the need for mechanical ventilation within 15 days from randomization 1. This parameter is counted as follows: D = zero (if the patient dies within 15 days (either in the hospital or at home or remains on respiratory support with oxygen through a nasal catheter, noninvasive ventilation, high-flow nasal catheter, or mechanical ventilation ≥ 15 days) D = 15 - x (if the patient is released from the hospital in < 15 days, where x represents the number of days with respiratory support during hospitalization)
Secondary objectives	Outcomes/secondary variables
Evaluate the status using the 7-stage ordinal scale for clinical outcomes on D15	Percentage of patients in various stages: 1. Not hospitalized with resumption of normal activities 2. Not hospitalized, but unable to resume normal activities 3. Hospitalized, with no need for supplemental oxygen 4. Hospitalized, requiring supplemental oxygen 5. Hospitalized, requiring high-flow nasal oxygen therapy, noninvasive mechanical ventilation, or both 6. Hospitalized, requiring blood oxygenation through a membrane system, invasive mechanical ventilation or both 7. Death
Evaluate the status using the 6-stage ordinal scale for clinical outcomes on D7	Percentage of patients in various stages: 1. Nonhospitalized 2. Hospitalized, with no need for supplemental oxygen 3. Hospitalized, requiring supplemental oxygen 4. Hospitalized, requiring high-flow nasal oxygen therapy, noninvasive mechanical ventilation, or both 5. Hospitalized, requiring blood oxygenation through a membrane system, invasive mechanical ventilation or both 6. Death
Evaluate 28-day mortality	Percentage of deaths in 28 days
Evaluate the number of days free from mechanical ventilation within 28 days	D = 28 - number of days requiring mechanical ventilation D = zero if death occurs or the patient continues to require mechanical ventilation after 28 days
Evaluate the number of days out of the hospital within 28 days	D = 28 - number of days after admission to the hospital D = zero if death occurs or the patient remains hospitalized after 28 days
Evaluate the time to discharge	Number of days from randomization to discharge, within 28 days D = 28 - number of days from randomization to hospital discharge D = zero if death occurs or the patient remains hospitalized after 28 days
Evaluate the number of days free of respiratory support within 15 days for Phases II/1 and II/2	D = 15 - number of days with respiratory support on hospitalization D = zero if death occurs or the patient remains hospitalized with a need for respiratory support defined as the use of low-flow, high-flow oxygen, IMV, or MV in 15 days
Safety objective	Outcomes/safety variables
Evaluate Grade 2, 3 or 4 adverse events, which were not present at the patient’s entrance, defined by the Division of AIDS table for Grading the Severity of Adult and Pediatric Adverse Events^(8)^	Percentage of Grade 2, 3, or 4 adverse events in the Division of AIDS table
Evaluate serious adverse events Percentage of serious adverse events	Evaluate discontinuation of study drug-related treatment Percentage of patients who needed to discontinue the intervention (study drug)

D - day; IMV - invasive mechanical ventilation; MV - mechanical ventilation.

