#### Phase III

The third stage of the study will proceed in a 2:1 allocation (two active treatments for each PbO), with a minimum inclusion of 189 patients and a maximum of 564. The study will perform interim analyses that may interrupt the study due to safety, futility, or efficacy, using all participants already randomized in Phases II/1 and II/2, since the primary efficacy outcome of Phase III (time of use of ventilatory support within 15 days) will be analyzed for all patients from these earlier phases as well.

The hypothesis test for the treatment effect will be performed using a generalized additive model of location and scale considering the distribution of a beta-binomial mixture with inflated zeros for the data adjusted by age and considering the random effect of the center for each intercept (model for the beta-binomial part and for the probability of zeros).

Phase III has three interim analyses planned, m = 3, for each third of the collected sample. The interim analyses consider stop limits according to the O’Brien-Fleming criterion, with significance levels of 0.06%, 1.51% and 4.71%, respectively, to maintain the global significance level at 5%. In Phase III, discontinuations due to futility will be allowed and use the same stopping criteria defined for efficacy.

Although the PbO group is composed of individuals receiving PbOs for three separate drugs (sometimes in combination), it will always be evaluated as a single group after gathering information from all “PbO arms”.

Secondary/exploratory outcomes and additional analyses are described in Supplementary material 1 (Section S4.1).

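### The Phase III primary outcome rule in Table 1 does not give every participant exactly one score that agrees with its own definition

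*Protocol article*

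**What the plan says.** Table 1 (Objectives) introduces the Phase III primary outcome as a count of support-free days. The definition it gives is "defined as the number of days without oxygen, noninvasive ventilation/high-flow nasal cannula or the need for mechanical ventilation within 15 days from randomization". A counting rule with two branches follows.

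- The zero branch begins "D = zero (if the patient dies within 15 days (either in the hospital or at home or remains on respiratory support". Its support clause ends, after naming low-flow oxygen, in "noninvasive ventilation, high-flow nasal catheter, or mechanical ventilation ≥ 15 days".
- The non-zero branch is "D = 15 - x (if the patient is released from the hospital in < 15 days". The article's explanation of the subtracted term is "where x represents the number of days with respiratory support during hospitalization".

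Further down, Table 1 lists the 15-day outcome for Phases II/1 and II/2 as a secondary outcome with its own rule. There the non-zero branch is "D = 15 - number of days with respiratory support on hospitalization". The zero branch, again with a 15-day horizon, is "D = zero if death occurs or the patient remains hospitalized with a need for respiratory support".

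The Phase III part of Analysis of primary outcomes labels the primary outcome "time of use of ventilatory support within 15 days". It says the outcome will also be analysed for patients from the two earlier stages, whose data enter the Phase III interim analyses. The model is a beta-binomial mixture with inflated zeros.

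**The concern.** A confirmatory endpoint must give each randomized participant one score and only one. Here the branches leave some survivors without a score, and for patients on oxygen at home the rule departs from the definition it is meant to implement. The unscored group (weaned but not discharged) is formed after randomization, so scoring or dropping these patients ad hoc could bias the comparison. The zero condition matters more than usual because the model has a separate part for the probability of zero.

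The endpoint also drives the Phase III stopping decisions for efficacy and futility, so an ambiguity left open now would have to be settled with data in hand.

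**Working it through.** **Inputs.** The scoring rules are those in Table 1. The group sizes come from Sample size: Phase II/1 has 189 active and 63 placebo, Phase II/2 has 126 active and 63 placebo, and Phase III has 376 active and 188 placebo.

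**Step 1: reproduce the article's pooled counts.** Placebo: 63 + 63 + 188 = 314. Treatment: 63 + 376 = 439 to 126 + 376 = 502. Total: 252 + 189 + 564 = 1,005. All agree with the article.

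**Step 2: apply each rule to hypothetical survivors.** The definition column is 15 minus all support days, in hospital or at home.

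| Course | Phase III rule | Phase II rule | Definition |
|---|---|---|---|
| A. Discharged day 8, 6 support days | 15 − 6 = 9 | 9 | 9 |
| B. In hospital at day 15, off support after 6 days | no branch | 15 − 6 = 9 | 9 |
| C. In hospital at day 15, off support after 14 days | no branch | 15 − 14 = 1 | 1 |
| D. Discharged exactly on day 15, 10 support days | no branch | 15 − 10 = 5 | 5 |
| E. In hospital at day 15, back on support, 12 support days in total | no branch if the 15 days mean duration; 0 if they mean status at day 15 | 0 | 15 − 12 = 3 |
| F. Discharged day 5 after 5 support days, home oxygen to day 15 | 15 − 5 = 10, and also 0 if the zero clause covers home | 10 | 15 − 5 − 10 = 0 |
| G. Discharged day 5 after 5 support days, 5 days of home oxygen | 10 | 10 | 15 − 5 − 5 = 5 |

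All the rules agree for the ordinary course A. Courses B to D are gaps in the Phase III rule. B and C are a state the trial expects: category 3 of its own day-15 ordinal scale is an inpatient who needs no oxygen. F and G conflict with the definition. E depends on how the zero clause is read.

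A death on day 4 scores 0 under both Table 1 rules. Taken literally as time on support it would be 4 days, a low value with no death rule attached.

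**Step 3: how much of each pooled arm comes from Phase II.** In the three-stage path:

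- placebo: (63 + 63)/314 = 126/314 = 40.1%
- treatment: 63/439 = 14.4% to 126/502 = 25.1%

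If phase-specific rules were used and moved the Phase II mean score by δ days in both arms, the raw difference in means between arms would shift by δ × (0.401 − 0.251) = 0.150δ to δ × (0.401 − 0.144) = 0.257δ. If Phase II/2 is skipped, the shares are 63/(63 + 188) = 63/251 = 25.1% and 63/439 = 14.4%, a shift of about 0.107δ. The article gives nothing from which δ could be estimated.

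**The case against.** Four counter-arguments deserve weight.

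- **Pooling.** A reader might infer that several non-equivalent definitions are pooled in one analysis. The article does not say that. It says the Phase III outcome will be analysed for the earlier patients, and on a plain reading the Phase III rule then applies to everyone. The Phase II rule belongs to a separate secondary outcome. This stands: a bias between arms follows only if phase-specific scores are used. But the Phase III rule has gaps, and the only 15-day rule listed for Phase II patients is the other one, so the matter is unresolved.
- **Zero conditions.** Both can be read as still being on support at day 15, and the Phase III cell has an unclosed parenthesis. This also stands: the wordings differ, but a difference in meaning is not proven.
- **The time-of-use label.** It is a parenthetical label, not a scoring rule. The abstract and Table 1 give days free of support, and Table 1 scores death as zero. A reader might infer that early death would count as favourable; Table 1 rules that out. It is a wording slip.
- **Condensation.** The article is shortened and refers to a SAP that is not shown. This does not dispose of the point, because the rule is stated in full and conflicts with its own definition. The Discussion also says the article is consistent with the approved protocol.

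It is also tempting to turn the unequal Phase II shares into a bias in days. That needs a proportion of affected patients and a score difference for them, and the article supplies neither. For course B the comparison is a score of 9 against no score, which is not a difference in days.

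**Conclusion.** The point holds for the Phase III rule itself. Survivors off support but in hospital at day 15, or discharged exactly on day 15, have no score. Patients on oxygen after discharge are credited with days that the definition excludes: 10 days in course F and 5 in course G. Home oxygen to day 15 may meet both branches at once.

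The wording in the Phase II row and in the Phase III analysis section is inconsistent with the rule and should be aligned, but neither shows by itself that different definitions are pooled. If phase-specific rules were used, the difference would not cancel, because Phase II supplies 40.1% of pooled placebo and 14.4% to 25.1% of pooled treatment in the three-stage path.

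The size of any bias cannot be estimated from the article. The conclusion does not depend on it: it rests on the text of Table 1 and on the hypothetical courses above, not on assumed frequencies.

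**What to change.** Before any Phase III analysis:

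1. State one scoring rule, in the same words, in the Phase III and Phase II rows of Table 1, and use it for all pooled patients. D is the number of days, from day 1 to day 15 after randomization, alive and without any listed support, in hospital or at home; D = 0 for death by day 15.
2. Delete the discharge condition and the restriction of x to hospital days.
3. State explicitly whether a patient on support at day 15 after earlier free days scores 0 or the free days accrued. The two answers give different outcomes, so this is a decision for the sponsor and not mere editing.
4. In the Phase III analysis section, replace "time of use of ventilatory support within 15 days" with days free of respiratory support.
5. Confirm that the post-discharge calls record home oxygen. As described under Retention, they cover adverse events and the ordinal scales, whose non-hospitalized categories do not record oxygen. The full form is not shown, so the item may already exist; if not, add it.

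The cost is wording in the protocol, with the SAP aligned to it, and at most one question on an existing telephone form.

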### Eligibility criteria

The inclusion and exclusion criteria are described in table 2. Procedures for the initial diagnosis of COVID-19, collection of biological material, viral identification, genetic sequencing and viral isolation in culture are explained in Supplementary material 1.

**Table 2 t2:** Inclusion and exclusion criteria

Inclusion criteria	Exclusion criteria
1. Adults (≥ 18 years) hospitalized with COVID-19 with one of the following conditions: - Positive RT-PCR test for SARS-CoV-2 OR - Typical clinical history AND chest CT with typical findings, pending the results of the RT-PCR test for SARS-CoV-2 2. Time between symptom onset and inclusion ≤ 9 days 3. SpO2 ≤ 94% in room air or need for supplemental oxygen to maintain an SpO2 > 94% 4. The patient consents to participate in the study and is willing to comply with all study procedures, including the collection of virology samples	Presence of any of the following conditions: - Patients requiring invasive mechanical ventilation - ALT or AST level > 5 times the upper limit of normal - Total bilirubin level > 2mg/dL - Platelet count < 50,000 cells/L - Total neutrophil count < 750 cells/L - Renal failure (eGFR < 30mL/min/1.73m^^2^^, using the MDRD or CKD-EPI method); and predefined renal failure Stage 3 according to the AKIN^(9)^ classification with a serum creatinine level > 4mg/dL or patient already on renal replacement therapy - History of liver disease with moderate to severe impairment (liver cirrhosis with - Child Pugh B and C classification) previously known* - Decompensated congestive heart failure* - Pregnant or breastfeeding patients - Known allergy or hypersensitivity to any study drug - Carrier of hepatitis C (positive HCV RNA), active hepatitis B (positive surface antigen in the past), or HIV (ELISA and confirmatory Western blot in the past) - Patients currently using nucleoside or nucleotide analog drugs for any indication - Corrected QT interval > 480 on the electrocardiogram - Heart rate < 55 bpm - Patients using or who recently used (< 90 days) amiodarone - Women of childbearing potential* or men with a partner of childbearing potential who do NOT agree to use two contraceptive methods (including barrier method) for 100 days

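### The time-to-discharge row of Table 1 gives two opposite scales: 28 minus days nearly repeats days out of hospital, and raw days has no valid value for deaths or patients still in hospital

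*Protocol article*

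**What the plan says.** In the protocol article, Objectives, Table 1, the secondary objective on time to discharge has one outcome cell with three statements:

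- a raw time, followed directly by a score: "Number of days from randomization to discharge, within 28 days D = 28 - number of days from randomization to hospital discharge";
- a rule for patients without a live discharge: "D = zero if death occurs or the patient remains hospitalized after 28 days".

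The row above, with the objective "Evaluate the number of days out of the hospital within 28 days", is scored as "D = 28 - number of days after admission to the hospital" and carries the same zero rule.

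The Outcomes section names Table 1 as the place where the secondary outcomes are defined. The Statistical methods section sends further detail on secondary outcomes to supplementary material, which is not at hand.

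**The concern.** The raw time and the score run in opposite directions: a low raw time is good, a low score is bad. The cell does not say which one is the analysis variable. Two analysts could both cite Table 1 and report results with opposite signs.

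Neither choice gives a usable time to discharge. The score handles death coherently, but it is no longer a time and largely repeats its neighbour. The raw time matches the row's name, but the cell gives it no handling of death or of continued stay. At stake is whether the trial reports time to discharge at all, and whether one result would be presented as two.

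**Working it through.** **Inputs from Table 1.** Let t be days from randomization to discharge. Raw scale: t. Score: D = 28 − t. For death or still in hospital after day 28: D = 0. Neighbouring row: 28 minus days counted from admission. If L is the lag from admission to randomization and there is no readmission, that is 28 − (t + L). Table 2 enrols patients who are already in hospital ("Adults (≥ 18 years) hospitalized with COVID-19 with one of the following conditions"), so L is zero or more.

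**Step 1: the two scales.** They agree only where t = 28 − t, that is at t = 14.

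| Discharge day t | Raw scale | D = 28 − t |
|---|---|---|
| 5 | 5 | 23 |
| 14 | 14 | 14 |
| 27 | 27 | 1 |
| Death, or in hospital after day 28 | no value given | 0 |

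**Step 2: the score against the row above.** The difference is (28 − t) − (28 − (t + L)) = L.

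- t = 5, L = 0: 23 and 23.
- t = 5, L = 2: 23 and 21.
- Death: 0 and 0.

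The documents do not give the distribution of L, so a range was simulated. Assumptions: gamma time to discharge (shape 2, scale 4.5, mean 9 days before rounding up to whole days), deaths of 5%, 10% or 20%, no readmission, and L spread evenly over the stated range.

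| Assumed lag (days) | Rank correlation of the two outcomes |
|---|---|
| 0 | 1.00 |
| 0 to 1 | 0.995 to 0.997 |
| 0 to 3 | 0.978 to 0.986 |

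**Step 3: the raw scale.** A patient who dies or is still in hospital at day 28 has no discharge within the window, so t does not exist. The only number in the cell for such patients is the zero, and it is assigned to D. Zero on the raw scale would lie below every discharge from day 1 onward.

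The zero rule therefore fits the score but not the row's name, and the raw time fits the name but not the zero rule.

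**The case against.** The strongest reply is that the cell follows a template. Mechanical-ventilation-free days, days out of hospital and the respiratory-support outcome are all scored as a window length minus days, with zero for death. On that view the first phrase only describes the quantity being subtracted, and the fault is a wrong label. A free-days score with death at zero is a legitimate outcome, correlated secondary outcomes are not an error in themselves, and competing-risk detail is commonly left to the analysis plan.

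Much of this stands. The score is the more natural reading, the overlap with the row above is near-exact and not literal, and the choice of hazard model can sit in the analysis plan. What does not fall away is the definition. Table 1 is the defining text, and any method given elsewhere would still have to choose between two opposite scales. If the template reading is right, the trial has no time-to-discharge outcome despite naming one.

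A reader might infer something stronger: that the plan scores deaths as the fastest discharges and so favours the arm with more deaths. The text does not support that, because the zero is written for D, where it is the worst value. Take an assumed mean of 10 days to discharge in survivors of both arms, all discharged by day 28, with deaths of 10% on placebo and 5% on active:

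- As written, on D (28 − 10 = 18 for survivors): 0.90 × 18 = 16.2 on placebo and 0.95 × 18 = 17.1 on active. The arm with fewer deaths looks better, as it should.
- Zero moved to raw days: 0.90 × 10 = 9.0 and 0.95 × 10 = 9.5. The arm with fewer deaths looks slower.

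The second result needs a step that the plan does not take. It shows only what would follow if an analyst kept the row's name and carried the zero across.

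**Conclusion.** The point holds as an inconsistent definition of one secondary outcome. Table 1 gives two scales that run in opposite directions and a zero rule that is meaningful on only one of them. Read as 28 minus days, the row is not a time to discharge and nearly duplicates days out of hospital: the scores are identical when there is no lag and no readmission, and otherwise differ by exactly the lag if there is no readmission. Read as raw days, it leaves deaths and patients still in hospital at day 28 without a valid value.

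The scale contradiction and the formula for the difference follow from the table's wording alone. The rank correlations rest on the assumed discharge times, death rates and lags. The supplementary material may name an analysis, but Table 1 would still need correcting.

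The consequence is limited. Stage changes depend on viral-load decay and safety, and Phase III efficacy on days free of respiratory support. No sample size or significance level involves this outcome, and 28-day mortality is reported separately. The change should be made, but the trial's main conclusions do not depend on it.

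**What to change.** 1. Keep the 28-minus-days score, with zero for death, only in the days-out-of-hospital row.
2. Define time to discharge as time from randomization to live discharge, censored at day 28, with death as a competing event. Report the cumulative incidence of live discharge by arm, with a subdistribution or cause-specific hazard ratio; the analysis plan can make that choice.
3. Remove the 28-minus-days formula and the zero rule from the time-to-discharge row.
4. If the sponsor prefers the score, the minimum is to state that one scale, rename the row accordingly, and acknowledge its overlap with days out of hospital.

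The cost is a wording change and a little more analysis work. No new data are needed: the existing 28-day outcomes already require discharge and survival status, and the plan has a day-28 contact. One difference should be noted when the change is made: a patient discharged alive who dies before day 28 scores zero on the present D but counts as a live discharge under the new definition. That death remains visible in 28-day mortality and in the days-out-of-hospital score.
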